## Abstract

**Background:**

Osteoarthritis (OA) of the knee is one of the main causes of musculoskeletal disability in the western world. Current available management options provide symptomatic relief (exercise and self-management, medication and surgery) but do not, in general, address the disease process itself. Moreover, adverse effects and complications with some of these interventions (medication and surgery) and the presence of co-morbidities commonly restrict their use. There is clearly a need to investigate treatments that are more widely applicable for symptom management and which may also directly address the disease process itself.

In two randomised controlled trials of four and 12 weeks duration, pulsed electrical stimulation was shown to be effective in managing the symptoms of OA of the knee. Laboratory and animal studies demonstrate the capacity of externally applied electric and electromagnetic fields to positively affect chondrocyte proliferation and extracellular matrix protein production. This latter evidence provides strong theoretical support for the use of electrical stimulation to maintain and repair cartilage in the clinical setting and highlights its potential as a disease-modifying modality.

**Methods/Design:**

A double-blind, randomised, placebo-controlled, repeated measures trial to examine the effectiveness of pulsed electrical stimulation in providing symptomatic relief for people with OA of the knee over 26 weeks.

Seventy people will be recruited and information regarding age, gender, body mass index and medication use will be recorded. The population will be stratified for age, gender and baseline pain levels.

Outcome measures will include pain (100 mm VAS and WOMAC 3.1), function (WOMAC 3.1), stiffness (WOMAC 3.1), patient global assessment (100 mm VAS) and quality of life (SF-36). These outcomes will be measured at baseline, four, 16 and 26 weeks. Activity levels will be measured at baseline and 16 weeks using accelerometers and the Human Activity Profile questionnaire. A patient global perceived effect scale (11-point Likert) will be completed at 16 and 26 weeks.

**Discussion:**

This paper describes the protocol for a randomised, double-blind, placebo-controlled trial that will contribute to the evidence regarding the use of sub-sensory pulsed electrical stimulation in the management of OA of the knee.

**Trial registration:**

Australian Clinical Trials Registry ACTRN12607000492459.

## Background

Osteoarthritis is a major cause of pain and disability in the community and OA of the knee is one of the most common causes of musculoskeletal disability in the Western world [1]. As prevalence increases it is expected to pose an increased burden on health care in the future.

Management options such as medication, exercise, self-management programs and surgery largely focus on providing symptom relief and maintenance of function, but do not, in general, address the disease process itself. Moreover, adverse effects and complications with some of these interventions (medication and surgery) and the presence of co-morbidities commonly restrict their use.

In recent years considerable effort has been directed towards investigating the effectiveness of putative disease-modifying OA drugs such as glucosamine, chondroitin sulfate, doxycycline and diacerein [2-5]. There is also interest in the use of pulsed electrical stimulation and electro-magnetic fields as potential OA disease modifying modalities. Laboratory work and animal studies provide theoretical support for the use of electrical stimulation to maintain and repair articular cartilage in the clinical setting [6-10]. However, there are limited studies examining the effects of pulsed electrical stimulation in humans.

Two randomised, placebo-controlled trials have reported using capacitively coupled pulsed electrical stimulation (PES) delivered via skin surface electrodes [11,12]. In both trials, outcome measures focussing on symptom relief and functional capacity have been the variables of interest.

The first of these trials [12] randomised 78 subjects to placebo or PES treatment with a monophasic, spiked signal at 100 Hz delivered by the Bionicare^® ^BIO-1000™. PES was applied for between six and 10 hours per day at an intensity just below the sensory threshold for four weeks.

Response to intervention was better for the active device than the placebo for the outcome measures of pain, physical function, physician global assessment and duration of joint stiffness in the morning (p < 0.05) [12]. No statistically significant difference was observed for range of knee joint motion, joint tenderness, joint swelling, knee circumference and 50 feet walking time.

The second PES trial [11] examined 58 subjects using the same stimulation device in the same manner over 12 weeks. In this trial significant and clinically meaningful results were reported in patient global assessment, a pain and symptom visual analogue scale, WOMAC function and stiffness and overall WOMAC score. Only WOMAC pain change between the placebo and active groups did not reach statistical significance.

No randomised, controlled trials studying this particular modality over a longer time period have been found.

The modality being investigated is neither invasive nor pharmaceutical. As the majority of those with OA of the knee are likely to be elderly, they are also more likely to have co-morbidities such as heart and lung disease which increase the anaesthetic risk associated with invasive surgery. Similarly, there is increasing awareness of the adverse side effects of many of the medications that are used to manage OA of the knee [13-15]. Consequently, in a climate where patients are seeking different options in their disease management strategies, the potential for PES to provide an effective, safe alternative that is acceptable to the community is very high.

This research proposes to investigate the longer term effectiveness of PES and to determine the sustainability of responses in subjects with symptomatic knee OA.

## Methods/Design

### Study design

A double-blind, randomised, placebo-controlled, repeated measure trial will be conducted over 26 weeks. Participants will be assessed, prior to the commencement of treatment (baseline), and after four, 16 and 26 weeks of treatment (Figure 1).

**Figure 1 F1:**
[figure not shown]
**Summary of study procedure**. ACR – American College of Rheumatology; WOMAC – Western Ontario and McMaster Universities Osteoarthritis Index; PGA – Patient Global Assessment; SF-36 – Medical Outcomes Study 36-item Short-Form Survey; HAP – Human Activity Profile; GPES – Global Perceived Effectiveness Scale.

### Aims and hypothesis

The primary aim is to investigate for a period of 26 weeks, the effectiveness of transcutaneous PES in the treatment of symptomatic knee OA. A secondary aim is to determine whether effects, if any, are influenced by gender, age and/or baseline pain levels.

The experimental hypothesis is that PES will produce a clinically important and sustained improvement in pain, function, patient global assessment, global perceived effectiveness, quality of life and activity levels when compared with placebo treatment in individuals with symptomatic OA of the knee.

### Participants

Seventy participants with primary OA of the knee will be recruited.

### Inclusion criteria

• Primary knee OA diagnosed in accordance with the American College of Rheumatology (ACR) modified clinical classification criteria (sensitivity 84%, specificity 89%) [16,17]. This classification system has been shown to be a valid tool for OA knee diagnosis [18].

• Persistent, stable pain for a minimum of three months.

• Pain score of at least 25 mm on a 100 mm visual analogue scale (VAS).

### Exclusion Criteria

• Co-existing inflammatory arthropathies.

• Contraindications to electrical stimulation (pregnancy, decreased sensory perception, presence of metal in the field of application, or any implanted electrical stimulation device).

• Skin disorders in the treated knee area.

• Scheduled to have a total knee replacement within six months of entering the trial.

• Not able to read or understand English.

### Procedure

#### Recruitment

Potential volunteers will be recruited through community-based rheumatology and general practices, rheumatology outpatient clinics in teaching hospitals in the Perth metropolitan area, the Arthritis Foundation of Western Australia and promotion through media outlets.

#### Determining eligibility and baseline assessment

Initially volunteers will be telephone-screened to check for obvious exclusion criteria.

At a screening visit, diagnosis according to the ACR modified clinical classification will be made, sharp/blunt sensory discrimination will be tested and the pain VAS completed. Eligible participants who present with bilateral OA of the knee will be asked to nominate which knee they consider to be the most symptomatic and that knee will be treated.

Subjects who meet eligibility criteria will receive further information concerning the trial. In particular, the aims and methods will be explained in detail following which, written consent to participate will be sought. This trial has been approved by the Curtin University Human Research Ethics Committee (HR122/2006). Following consent, participants will be assigned an identification number and will be asked to complete baseline measures of WOMAC pain, stiffness and function, patient global assessment, quality of life and the Human Activity Profile (HAP) test, while details regarding body mass index (BMI), age, gender, laterality of joint disease, disease severity (if X-ray available) and current medication will be recorded. Participants who have not had a plain X-ray within the past two years will be referred for X-ray. Participants who are unwilling to have X-rays taken will not be excluded from the trial. Available X-rays will be graded according to the Kellgren and Lawrence radiological grading system. All outcome measurements will be taken and all instructions provided by an experienced musculoskeletal physiotherapist at Curtin University of Technology. At this first visit participants will also be provided with an accelerometer to collect seven days of ambulatory activity, after which it will be returned in person.

In the interim, participants will be randomly allocated into groups. Upon returning the accelerometer, they will be fitted with the PES device and given detailed verbal and written instructions regarding its use. They will also be provided a medications diary and relevant instructions.

### Randomisation and blinding

An administrator, not otherwise involved with the trial, will allocate the participants to groups using computer-generated block randomisation combined with stratification. Groups will be stratified with regard to gender, age (<60, 60–75 and >75), and intensity of pain (VAS scores 25–40, 41–60 and 61–100). The administrator will dispense an appropriate device using a list, provided by the senior biomedical engineer who modified the devices, that matches the device serial numbers to active or placebo. Participant identification will be added to the list at the time of randomisation so, should the need arise, the investigators will be able to determine the nature of the device provided to a participant without risk of becoming aware of assignment for any other participants (Figure 2). The measurer though will remain blinded to assignment throughout.

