### Sample Size Calculations

The primary outcome measure will be defined as an improvement in the absolute pain VAS score of 20. This is the minimum absolute change necessary for classification as a responder in the Osteoarthritis Research Society International (OARSI) response criteria [32,33]. Assuming no change in the placebo group, it has been calculated that a sample size of 70 (35 in each group allowing for 20% withdrawals) will be sufficient to detect this 20 point change as well as differences equal to the absolute minimal clinically important improvements of 19.9 (Pain VAS), 18.3 (PGA) and 9.1 (WOMAC function) described by Tubach et al [34] with a power of 80% using a two-tailed test with alpha level of 0.05. Calculations were based on standard deviations data from Garland et al [11] (Pain VAS and PGA) and Raynauld et al [35] (WOMAC function).

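### Blocking 70 participants within 18 gender-by-age-by-pain strata gives up part of the balance the scheme is meant to secure; minimisation would keep more of it at little cost

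*Protocol article*

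**What the plan says.** Under Randomisation and blinding, an administrator outside the trial allocates participants by "computer-generated block randomisation combined with stratification". The factors follow: "Groups will be stratified with regard to gender, age" (under 60, 60–75 and over 75) and pain on the VAS (25–40, 41–60 and 61–100). The method is therefore permuted blocks within the cross-classification of all three factors. The text gives no block size, and the figure showing the process is not reproduced in the copy at hand.

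The Participants section sets the size: "Seventy participants with primary OA of the knee will be recruited". Sample Size Calculations plans "35 in each group allowing for 20% withdrawals", "with a power of 80% using a two-tailed test with alpha level of 0.05".

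Two other sections bear on the point. Aims and hypothesis sets a secondary aim of learning whether any effect depends on gender, age or baseline pain, so all three stratifiers have a purpose. Statistical Analysis compares change in pain from baseline to 26 weeks by an independent t-test, and adds a linear mixed model that adjusts for baseline.

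**The concern.** Permuted blocks guarantee equal numbers only in completed blocks. A stratum that stops partway through a block can leave one arm ahead, and these remainders add up across strata. With few people per stratum, much of the sample sits in unfinished blocks.

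At stake are the evenness of the two arms and their balance on each factor, pain above all. The t-test on change in pain does not adjust for baseline level or stratum, so a chance imbalance in pain passes into that comparison. The secondary aim also works best when each band holds similar numbers from both arms.

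**Working it through.** **Inputs from the article.** N = 70; 35 per arm including 20% withdrawals; gender 2 levels, age 3, pain 3; target difference 20 mm; 80% power; two-sided 5%.

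**Assumptions.** Block sizes of 2, 4, 6 and 8. Factor mixes either even or uneven (gender 40/60 or 35/65; age 30/50/20; pain 30/40/30 or 35/40/25). For baseline pain in mm, values are uniform within bands, with the top band cut at 85. Both kinds of mix gave nearly the same results.

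**The plan's own figure.** 28 / (1 − 0.20) = 35 per arm, so the withdrawal step is consistent. The SDs are not given, so the 28 cannot be reproduced.

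**Stratum size.** 2 × 3 × 3 = 18 strata; 70 / 18 = 3.9 people each.

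**Simulation.** Each simulated trial places 70 people in strata at random and applies permuted blocks within each stratum. For simple randomisation, the SD of the arm-size difference is √70 = 8.4.

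| Scheme | Strata ending on an unfilled block | Opened blocks left unfilled | SD of arm-size difference | Split 32:38 or worse | Some pain band differs by 4 or more | SD of baseline pain difference (mm) |
|---|---|---|---|---|---|---|
| 18 strata, block 2 | about 9 | 23% | 3.0 | 9% | 11% | 2.0 |
| 18 strata, block 4 | about 14 | 56% | 3.9 | 19–20% | 31–32% | 2.3 |
| 18 strata, block 6 | 15–16 | 77–82% | 4.7–4.8 | 29–30% | 48–50% | 2.7 |
| 18 strata, block 8 | 16–17 | 89–96% | 5.2–5.7 | 35–38% | about 60% | 2.9–3.1 |
| Simple randomisation | – | – | 8.4 | 54–56% | 85% | 4.1–4.3 |

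**Share of chance variance in baseline pain removed,** against simple randomisation (even mix):
- block 4: 1 − (2.29/4.32)² = 72%
- block 8: 1 − (3.05/4.32)² = 50%
- stratifying on pain alone, block 4: 1 − (1.56/4.32)² = 87%

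**Power.** With 28 v 28 completers, 80% power for 20 mm implies an SD of 26.7 mm. Power is Φ(20 / (26.7 × √(1/n₁ + 1/n₂)) − 1.96):
- 25 v 31: 79.5%, a loss of 0.5 points
- 23 v 33: 78.7%, a loss of 1.3 points

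An arm-size difference of 10 or more arises in 0.2%, 1–2%, 6% and 9–12% of trials at blocks of 2, 4, 6 and 8.

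**Minimisation.** Each person goes, with probability 0.9, to the arm that reduces the summed imbalance over gender, age band and pain band. The arm-size SD is 1.3. A gap of 4 or more occurs in about 4% of trials for pain, 4% for age and 2% for gender. This beats the 18-stratum scheme on every measure at every block size tried. With probability 0.8 the gain is smaller: the arm-size SD is 1.8 and pain-band gaps of 4 or more occur in about 14% of trials. That is better than blocks of 4 or more, but not better than blocks of 2 on age and pain bands.

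**The case against.** The strongest reply is that the loss depends on a block size the article does not give. An article commonly leaves block size to the full protocol, so its absence is not a fault. At block 2 only 23% of opened blocks stay unfilled and a 32:38 split occurs in 9% of trials. This stands: a reader might infer that most blocks never fill, but that follows only from block 4 upwards.

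A reader might also infer that the scheme loses much of its balance on baseline pain, or fails to secure it. That goes too far. Unfilled blocks still balance in part: at block 4 the scheme removes 72% of the chance variance, and the excess over pain-only strata is about 0.7 mm (2.3 against 1.6) on a 100 mm scale. Only at blocks of about 6 to 8 is the loss large.

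Nor is the result biased. The t-test on change stays valid under chance imbalance, the mixed model adjusts for baseline, and 35 per arm is a planning figure. Nothing in the article says that baseline pain is the main predictor of change; it is only a stratifier and a possible effect modifier.

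Finally, using fewer strata has its own price. Blocking on pain alone roughly doubles the chance of an age-band gap of 4 or more at block 4, from 31% to just over 60%, and the secondary aim needs age and gender balance too. That objection defeats pain-only stratification but does not touch minimisation, which serves all three factors.

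**Conclusion.** The point holds as a minor one of efficiency. Eighteen strata are too many for 70 people under permuted blocks, and some balance in arm size and in each factor is lost for no gain. The direction holds at every block size and factor mix tried; the size does not, because the block size is unknown. The chance of a pain-band gap of 4 or more runs from about 11% at block 2 to about 60% at block 8. Validity is intact, the scheme remains well ahead of simple randomisation, and the power cost is 0.5 points for a difference of 6 completers and 1.3 for the less common difference of 10. The baseline-adjusted mixed model lessens the harm; the unadjusted t-test does not. The figures rest on the assumed block sizes, factor mixes and spread of pain scores.

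**What to change.** For participants not yet randomised, have the same independent administrator allocate by minimisation with a random element on gender, age band and pain band. A probability near 0.9 is preferable to 0.8 if the full protocol turns out to use blocks of 2. Start the routine from the counts of those already allocated, and include the three factors in the mixed model.

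The cost is setting up and testing a routine; no extra participants or visits are needed. Timelines for E-PES trial says that final screening and data collection began in October 2007, so this may be a mid-trial change. The date and the number already randomised would then have to be documented. If few participants remain to be randomised, the change to allocation brings little, and adding the factors to the model is the part still worth making.

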**Figure 2 F2:**
[figure not shown]
Process for stratified randomisation and concealed allocation.

The group-to-device-to-intervention code will remain in the possession of the equipment dispensary (protected by password) until after the data analysis has been completed.

### Trial intervention

A commercially available transcutaneous electrical nerve stimulator (Metron Digi-10s) has been adapted by a senior biomedical engineer to produce either a pulsed, exponentially declining waveform with a frequency of 100 Hz or a placebo device identical in appearance. Participants will be advised to use the device at a sub-sensory level, to replicate the conditions in the previous randomised controlled trials, for a minimum of seven hours per day. It will be recommended that they wear the device overnight. There is a locking mechanism on the device so that once the treatment intensity has been set there can be no inadvertent intensity change during the course of treatment. The instructions given to participants by the physiotherapist, who remains blind to the nature of the device, will be exactly the same regardless of which device participants are using.

### Background therapy

Participants will be asked to continue their normal background medical management during the trial period. A medications diary will be used to alert the investigators to any changes in medication usage. Each subject's managing doctor will be informed by letter of their patient's participation in the trial. Doctors will be requested to refrain from changing OA management during the period of the trial if at all possible.

### Compliance

Participants will be asked to keep a record of their daily PES use. This will be maintained within the medications diary booklet. Intermittent questioning about PES use via regular phone calls during the trial period and a review of the booklet at 16 weeks will occur.

### Safety monitoring and adverse events

Participants will be encouraged to contact the investigators should any questions arise during the trial. Correspondingly, they will be asked open-ended questions by the physiotherapist during the scheduled phoned calls to determine any adverse effects from using the device. The only adverse reaction that is expected is mild skin irritation. This occurred in both the placebo and intervention groups in both randomised controlled trials in approximately equal proportions (range 17.9–24% active and 21 – 21.1% placebo) and responded favourably to topical therapy, a temporary halt in use and/or change in the conduction gel [11,12]. Any participant reporting skin irritation will be asked to stop using the device and to return to the Curtin University School of Physiotherapy for assessment at the first available opportunity. Should there be pain, swelling or more than a five centimetre diameter area of redness after desisting for 48 hours, a medical opinion will be obtained before proceeding further.

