## Discussion

This paper describes the rationale and protocol for conducting a double-blind, randomised, placebo-controlled trial that will investigate the use of pulsed electrical stimulation in the management of OA of the knee. It incorporates features designed to minimise bias [37] and uses valid outcome measures that will facilitate comparability with other research in the area.

This trial will contribute to the evidence regarding the use of a non-pharmaceutical, non-invasive modality in managing symptoms of OA of the knee. Given the modality's simple technology and ease of use (patients can readily use it at home), it has huge potential to provide a safe, effective treatment option for clinicians.

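### Harms are elicited as effects of using the device, so events nobody links to it have no stated route into the record of a longer exposure than the cited trials covered

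*Protocol article*

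**What the plan says.** All places are in the Protocol article.

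- **Safety monitoring and adverse events.** The active route is the telephone call: "they will be asked open-ended questions by the physiotherapist during the scheduled phoned calls to determine any adverse effects from using the device". Participants may also make contact themselves: "Participants will be encouraged to contact the investigators should any questions arise during the trial". The expectation is stated as "The only adverse reaction that is expected is mild skin irritation", with earlier rates given as "range 17.9–24% active and 21 – 21.1% placebo". The follow-up path described is for skin irritation.
- **Background therapy and Compliance.** "A medications diary will be used to alert the investigators to any changes in medication usage". The same booklet holds the record of daily device use.
- **Trial intervention.** The device is an adapted Metron Digi-10s, to be used "for a minimum of seven hours per day", and overnight wear is recommended. The physiotherapist giving instructions is blind to the type of device.
- **Background.** The first earlier trial used the Bionicare BIO-1000 for four weeks: "PES was applied for between six and 10 hours per day". The second is described as using the same device in the same way for 12 weeks. The authors found no longer randomised trial of this modality.
- **Study design.** Participants are followed for 26 weeks, with assessments at baseline and at 4, 16 and 26 weeks.

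**The concern.** The strength of a blinded, placebo-controlled trial for harms is that nobody has to decide, case by case, whether an event came from the device. Events of every kind are collected in both arms, and the comparison between arms shows which are in excess. If the question put to participants concerns effects of the device, part of that causal judgement moves forward to the moment of collection, where it is least reliable.

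The events most at risk are those with an obvious alternative explanation. The Background expects many patients with this condition to be elderly and to have heart and lung disease. Poor sleep or a fall at night in such a person is easily put down to age or to the knee, even when a device is being worn overnight. Skin irritation under an electrode is hard to miss. The record is therefore likely to be most complete for the one reaction already expected, and thinner for anything unexpected.

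The choice cannot be repaired later. An analysis plan can tabulate what was recorded, but not what was never asked about.

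**Working it through.** **Step 1. Does any stated route collect events regardless of cause?**

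| Stated route | What it is for | Covers events not linked to the device? |
|---|---|---|
| Scheduled calls | Open-ended questions aimed at effects of the device | Not by its stated purpose |
| Participant-initiated contact | Questions that arise | Not set up as event reporting |
| Medications diary | Changes in medication | Only if the event changes medication |
| Device-use record in the same booklet | Daily use | No |
| VAS, WOMAC, patient global assessment, SF-36, GPES | Knee symptoms, function, global state, quality of life | A worse knee, yes; a discrete event such as a fall, no |

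The term open-ended describes the form of the question; the reference to the device sets its scope. No row is a general route for adverse events.

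**Step 2. What does this do to the comparison?** Suppose an event has true proportions pA (active) and pP (placebo), and a fraction c is captured. Blinding and identical questioning make it reasonable to take c as equal in the two arms. Then

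observed difference = c × pA − c × pP = c × (pA − pP).

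With c below 1 the comparison is still fair, but the absolute excess shrinks and rests on fewer events. The document gives nothing from which to estimate c, so I put no figure on the loss.

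**Step 3. How far does the exposure go beyond the source of the expectation?**

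Inputs: 26 weeks (Study design); at least 7 hours a day (Trial intervention); 4 and 12 weeks (Abstract, Background); 6–10 hours a day (Background, stated for the first trial and applied to the second because it is said to have used the device in the same manner).

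Hours = weeks × 7 days × hours per day.

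- This trial, minimum: 26 × 7 × 7 = 1,274 h
- 4-week trial: 4 × 7 × 6 = 168 h to 4 × 7 × 10 = 280 h
- 12-week trial: 12 × 7 × 6 = 504 h to 12 × 7 × 10 = 840 h

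Ratios in hours:

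- against 12 weeks: 1,274/840 = 1.5 to 1,274/504 = 2.5
- against 4 weeks: 1,274/280 = 4.6 to 1,274/168 = 7.6

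Ratios in calendar time: 26/12 = 2.2 and 26/4 = 6.5.

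These are planned hours, not hours achieved. The document states no figure of its own for cumulative exposure or for precision on harms, so there is none to reproduce.

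**Step 4. Is the difference stated where the rates are used?** The durations appear in the Abstract and Background, and the earlier device is named in the Background. The safety section quotes the irritation rates without either qualification.

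**The case against.** The best defence is that the sentence gives the purpose of the call, not a recording rule. The questions are open-ended, their actual wording is not shown, and nothing says that a participant must attribute an event to the device before it is noted. That is right as far as it goes. A reader might infer that only participant-attributed effects are recorded; the text does not say so. What stands is narrower: the stated purpose is limited by cause, and no other route is stated for events outside it.

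Further points in the plan's favour:

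- **Both arms are treated alike.** Instructions are the same in both arms and the physiotherapist is blind, so whatever is elicited remains comparable. I accept this. The loss is in completeness, not in fairness between arms.
- **A worse knee is not missed.** VAS, WOMAC and patient global assessment at 4, 16 and 26 weeks, and GPES at 16 and 26 weeks, would show it.
- **Using earlier trials for expectations is normal.** The authors report finding nothing longer. The rates only need to be labelled with their source conditions.

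Some stronger readings are tempting but unsupported:

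- **Harms will not be compared by arm.** Statistical Analysis lists no such comparison and harms are not among the outcome measures, but an article may leave both to a full protocol or analysis plan that is not shown.
- **The trial anticipates a long-term safety conclusion.** The Discussion says "it has huge potential to provide a safe, effective treatment option for clinicians" and the Background likewise speaks of potential; the stated aim is effectiveness.
- **Daily use contradicts the earlier trials.** Seven hours lies within 6–10, and an unstated upper limit is not a contradiction.
- **Small-sample limits measure this defect.** With no events of a kind among 35 participants, the two-sided 95% upper limit is 1 − 0.025^(1/35) = 10.0%. That reflects the sample size, and no rewording of questions would change it.

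**Conclusion.** The point holds as a cheap improvement to data collection. The safety section limits the stated purpose of questioning to effects of the device, and no other described route takes in events regardless of cause. This weakens the blinded comparison of harms over a planned exposure of at least 1,274 hours, which is 1.5–2.5 times that of the 12-week trial and 4.6–7.6 times that of the 4-week trial, on a different device.

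The ratios assume that the advised minimum is met on every day for 26 weeks and that the 12-week trial used the same 6–10 hours a day as the 4-week one. The size of the loss itself is unknown. It depends on the wording used on the calls and on how often participants and the physiotherapist would fail to connect an event with the device.

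The efficacy analyses are unaffected. The document should not be read as shutting out unattributed events altogether, as leaving harms uncompared between arms, or as promising a demonstration of long-term safety.

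**What to change.** In Safety monitoring and adverse events:

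1. Have the blinded physiotherapist ask, at each scheduled call and at the existing 4-, 16- and 26-week assessments, about any new or worsened health problem since the last contact, whatever its presumed cause.
2. Judge relatedness to the device as a separate step, while still blinded.
3. Add one sentence saying that the irritation rates (17.9–24% active, 21–21.1% placebo) come from 4- and 12-week use of another device, and that this trial plans a longer exposure.

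The cost is a reworded question at contacts already scheduled, one added sentence and a minor amendment. No extra visits or participants are needed. The downside is that more unrelated events will be recorded and will need a relatedness judgement. The wording should be in place before further follow-up, because events not asked about cannot reliably be reconstructed later.
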